#### Analyses of effect

Establishing a baseline in 2015 permits a paired comparison of results in 2016, meaning one-year effect analyses of intervention on multiple variables as described in Table 2. The analyses would include test *within-subject* variation as well as *between-subject* variation for both intervention and control schools using basic univariate parametric tests as e.g. t-tests, linear or logistic regression analysis and linear mixed models for repeated measurements. Possible confounding, mediation and/or effect modification will be assessed using stratified and multivariable statistical models and statistical methods for causal inference (e.g. Directed Acyclic Graphs).

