**Methods:**

The HOPP study is a 7 years longitudinal large-scale controlled intervention in seven elementary schools (*n* = 1545) with two control schools (*n* = 752); all aged 6–11 years at baseline. The school-based physical activity intervention program includes an increase in physical activity (PA) of 225 min/week as an integrated part of theoretical learning, in addition to the curriculum based 90 min/week of ordinary PA. Primary outcomes include cardio-metabolic risk factors measured as PA level, BMI status, waist circumference, muscle mass, percent fat, endurance test performance, total serum cholesterol, high-density lipoprotein (HDL), non-HDL, micro C-reactive protein (mCRP) and long-term blood sugar (HbA1c). In addition, secondary outcomes include anthropometric growth measures, physical fitness, quality of life (QoL), mental health, executive functions, diet and academic performance.

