##### 8) Oxygen uptake

Only pupils born 2008 are to be tested for oxygen uptake annually until 2021 as oxygen uptake procedures require use of highly sophisticated instruments for field-testing and is time consuming. By obtaining seven consecutive years of data, longitudinal measurement of physiological development across childhood will be available. In addition, the design permits comparison between intervention (*n* = 248) and control (*n* = 103) schools for all years.

The oxygen uptake test at baseline was performed on a treadmill (Matrix T3xe, USA) measuring peak oxygen uptake (VO_2peak_), respiratory rate (RR), respiratory exchange ratio (RER), peak ventilation (VE_peak_), peak heart rate (HF_peak_) and time to exhaustion using a portable metabolic analyzer, Cosmed K4b^2^,(Cosmed S.r.l., Roma, Italia). A Hans Rudolph V2 oro-nasal facemask (Hans-Rudolph, Shawnee, KS, USA) was used during testing. The protocol in use had a start load of 5 km/h – 5% incline for 5 min. The speed was increased to 7 km/h, and further by 1 km/h every minute until reaching 10 km/h. After this point, a 1% increase in incline was applied every minute until fatigue [30, 31]. Breath by breath results was averaged to 30 s intervals and the highest 30 s value near the end of the test was considered the VO_2peak_. As test termination criteria for adults are difficult to achieve for children, the children’s unwillingness to continue was used as an indication of VO_2peak_ [32].

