##### Intervention analyses

Annually analyses between intervention and control schools in numerous variables, the sample size for a parallel group design is calculated using *n* = 2 • (σ / Δ) ^2^ • *k* [26]. Here n represents the number of participants in each group, σ (sigma) is the expected standard deviation of the observations (which are assumed equal for all groups), Δ (delta) gives us the relevant difference between observations, and k is the constant in this study chosen based on the common values by a double-sided t-test set at 5% and with test strength 80% (this corresponds to a *k* of 7.9) [26]. Based on these calculations we have determined the sample size to be adequate for all variables for all ages, also when divided into gender (Table 3).

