#### Analyses of longitudinal effect

The longitudinal intervention design allows for exploratory analysis of group means over time to discover patterns of systematic variation across groups, as well as among individuals. The design allows for analyses of age and growth effects [50]. As the eldest pupils enrolled at baseline 2015 finish elementary school in 2016, only one year of follow-up is possible. However, an increasing number of years of follow-up are possible with decreasing age at enrolment. This allows for an adjustment of the longevity of being enrolled in the program, and hence measurement of the time-in-the-program effect. Secondly, an annual comparison between the intervention schools and the control schools allows for testing of effect of the intervention. Thirdly, mean values across test time allows for time slopes showing possible effect as an interaction (i.e. effect modification) of intervention and time. A different approach for test across test time may be pre-post analysis of a single follow-up response in conjunction with a baseline measurement [50]. Fourthly, an annual comparison with the upcoming grade within the intervention schools allows for analyses of secular trends.

The longitudinal design in the HOPP study with repeated measures allows for use of a linear mixed regression model using test-year, years of follow-up, intervention versus control school, age and gender as fixed factors for the main outcome of cardio-metabolic risk factors. A similar model may be used for secondary outcomes of academic performance, PA level, cognitive performance, as well as medical and physical results, and simultaneously controlling for baseline values. In addition, the design admits analyses of interaction (i.e. effect modification) between type of intervention group and number of years in intervention.

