### Limitations of the study

One challenge with all longitudinal designs, is dropout as the participants decline completing the intervention or do not show to tests. In addition to regular dropouts, the HOPP study has a decreasing number of participants as the children are transferred to junior high school. This design have two major implications: ^1)^ the amount of years the pupils are in the intervention varies depending on the age at inclusion. Children born in 2003 only participate one year before exit. Those born 2004 are enrolled in two years, born 2005 in three years, and so forth. This implies challenges regarding the statistical analyses, as results from pupils with fewer years in intervention must be weighted less than pupils with additional years. ^2)^ Due to age-specific tests not all children receive all tests. In those tests only a limited amount of participants are to be analysed in an effect of intervention. Instead secular trends are to be used.

A major challenge in all interventions is compliance, and in the present study the teacher’s compliance is essential. Encouraging teacher’s to complete the intervention every day is a major challenge, and is taken care of by Horten municipality. Two designated teachers at each school as well as a centralised coordinator, performed daily encouragements as well as written control of participation. The individual compliance of each pupil is more difficult to survey. The participation rate as being part of the class is registered using reports of absence from school. However, in what extent and what intensity each pupil performed each task are more difficult to control.

Due to Horten municipality decision on giving all schools in the municipality the same school-based PA program, a randomised controlled trial was not possible. However, using control schools with corresponding socioeconomic status, a controlled design was used.

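### The programme goes to whole schools (7 versus 2), but the sample size is justified as if pupils were independent, and no school or class term is named in the analyses

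*Protocol article*

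**What the plan says.** The section on limitations explains the allocation: "giving all schools in the municipality the same school-based PA program, a randomised controlled trial was not possible". The abstract gives seven intervention schools with 1545 pupils and two control schools with 752. The section on the study population places the two groups in different counties.

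The section headed Intervention analyses uses n = 2(σ/Δ)²k, with k = 7.9 for a two-sided 5% test at 80% power. It defines the unit plainly: "Here n represents the number of participants in each group". No σ, Δ, ICC or design effect is given. Table 3 lists sizes from 10 to 126, obtained from one-sample t, two-sample t and Z-score calculations. The section then concludes that the sample suffices for all variables and ages, including after a split by gender.

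For the one-year effect, the section Analyses of effect lists methods, "using basic univariate parametric tests as e.g. t-tests, linear or logistic regression analysis and linear mixed models for repeated measurements". The longitudinal section says that the design allows a linear mixed model with test-year, years of follow-up, "intervention versus control school, age and gender as fixed factors for the main outcome of cardio-metabolic risk factors". The list of limitations covers dropout, unequal time in the programme, compliance and the lack of randomisation, but not clustering.

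**The concern.** Pupils in one school share teachers, facilities and catchment, and the lessons are run class by class at the teacher's discretion. Their outcomes are therefore likely to be positively correlated. With only two control schools, the control mean rests on two school-level values, however many pupils are measured.

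A mixed model for repeated measurements deals with correlation between the yearly values of one child. It does not deal with correlation between different children in one school. A fixed factor for intervention versus control estimates the arm effect and likewise does not absorb variation between schools within an arm.

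Two things are at stake: the error rate of any pupil-level arm comparison, and the statement that the stated power holds for every age and gender.

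**Working it through.** **Inputs from the protocol.** Pooled: 1545 pupils in 7 schools and 752 in 2, so mean school sizes are 1545/7 = 220.7 and 752/2 = 376. Grade 1, from Table 1 and the oxygen-uptake section: 248 and 103, or 35.4 and 51.5 per school. Blood samples: 58.4% of pupils at baseline. Two-sided alpha 5%, power 80%.

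**Assumptions.** ICC of 0.01, 0.02 or 0.05; equal school sizes within arm; no covariate or baseline adjustment; the same 58.4% in both arms for blood samples (about 902 and 439); one gender is half of a grade (124 and 51.5).

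**Step 1: the plan's own figures.** k = (1.960 + 0.842)² = 7.85, which agrees with the stated 7.9. The sizes in Table 3 cannot be rebuilt directly because σ and Δ are not given. They do match ordinary uninflated calculations:
- The exact two-sample t-test at 0.5 SD needs 63.8, so 64 per group (the anthropometry entry).
- The formula gives 2 × 7.85/0.25 = 63 per group, or 126 in total (the cardio-metabolic entry).
- A one-sample t-test at 0.5 SD needs about 34, and at 1.0 SD about 10.

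None of these contains a cluster inflation.

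**Step 2: variance of the arm difference.** In units of σ², the pupil-level value is 1/n_I + 1/n_C. With clustering it is D_I/n_I + D_C/n_C, where D = 1 + (m − 1) × ICC and m is the mean school size in that arm.

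Pooled sample at ICC 0.02:
- D_I = 1 + 219.7 × 0.02 = 5.39 and D_C = 1 + 375 × 0.02 = 8.50.
- Clustered variance = 5.39/1545 + 8.50/752 = 0.01479.
- Pupil-level variance = 1/1545 + 1/752 = 0.00198.
- Ratio = 7.5.

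**Step 3: type I error of a nominal 5% pupil-level test** = 2 × [1 − Φ(1.96/√ratio)].

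| Sample | Ratio at ICC 0.01 / 0.02 / 0.05 | Type I error |
|---|---|---|
| Pooled baseline | 4.2 / 7.5 / 17.2 | 34 / 47 / 64% |
| Blood-sample subset | 2.9 / 4.8 / 10.4 | 25 / 37 / 54% |
| Grade 1 | 1.5 / 1.9 / 3.3 | 10 / 16 / 28% |

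**Step 4: effective size.** The pooled sample is worth 483 / 286 / 129 independent intervention pupils and 158 / 88 / 38 controls. The control figure can never exceed 2/ICC, that is 200 / 100 / 40.

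**Step 5: power at 0.5 SD.** The non-centrality is 0.5/SE, with SE the square root of the clustered variance. There are 9 − 2 = 7 degrees of freedom (critical t 2.365). For grade 1 at ICC 0.02, SE = √(1.689/248 + 2.010/103) = 0.162, the non-centrality is 3.08 and power is 75%.

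| Sample | Independent pupils | Clustered, normal approximation | Clustered, t on 7 df |
|---|---|---|---|
| Grade 1 | 98.9% | 94 / 87 / 65% | 86 / 75 / 53% |
| Grade 1, one gender | 85.5% | 78 / 71 / 54% | 65 / 58 / 43% |

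For the pooled sample on 7 df, power is at least 94% at ICC 0.01 and 0.02, and about 65% at 0.05.

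**The case against.** Four stronger readings are tempting, and the document does not support them.

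- **That cluster adjustment is ruled out.** The longitudinal section says what the design allows and lists only fixed factors. It gives no random-effects structure, not even one for the pupil. The list in Analyses of effect is illustrative and also covers within-subject change. A school term is not named, which is different from excluded, and a full analysis plan may contain one.
- **That every named method treats all observations as independent.** The repeated-measures model does handle correlation within a child. The gap is correlation between children of one school.
- **That the whole study is underpowered.** The pooled sample could detect about 0.125 SD if pupils were independent (2.80 × √(1/1545 + 1/752)), but the protocol never claims that target. Against the 0.5 SD that Table 3 implies, the pooled comparison remains adequate up to an ICC of about 0.02.
- **That the error rates of 34% to 64% are those of the main outcome.** They are for the pooled, unadjusted baseline sample. The composite needs blood values, so the subset figures are closer, and older cohorts leave each year. Baseline adjustment, which the protocol mentions, could lower the ICC further.

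Recruitment is complete and the municipality fixed the number of intervention schools, so the sizing error cannot now change the design.

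What stands is that the adequacy statement has already been drawn from an individual-level formula, and a later plan cannot make that reasoning right. The text on effects also gives an analyst no instruction to account for schools, and offers plain t-tests.

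**Conclusion.** The point holds. The sample-size justification ignores that whole schools receive the programme, and the published analysis text names no means of accounting for it. The direction is certain for any positive ICC. The size depends on the ICC, which the document does not give, and on the equal school sizes and absence of adjustment assumed here.

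Over ICC 0.01 to 0.05, a pupil-level test would reject a true null far more often than 5%, and most often in the pooled sample because its clusters are largest. The power statement fails first where the protocol extends it furthest. For one gender within grade 1, power is below 80% at every assumed ICC, even with the normal approximation. For the whole of grade 1 it falls below 80% from 0.02 on 7 df. The 0.5 SD is back-solved. If the cardio-metabolic entry of 126 is read per group, the implied difference is √(2 × 7.85/126) = 0.35 SD, and power would be lower throughout.

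**What to change.** **Analysis.**
- In linear arm comparisons, include a random effect for school, and for class where it can be identified. Nest pupil within these for repeated measures, and use a small-sample degrees-of-freedom correction such as Kenward-Roger. Comparing school-mean changes on 7 df is a simple alternative.
- For binary outcomes that correction does not carry over. Use school-level summaries, or a cluster-aware method with a correction for few clusters.
- Do not use plain pupil-level t-tests to compare arms.

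**Sample size.** Replace the adequacy statement under Intervention analyses with detectable differences for nine schools over a stated ICC range, for the pooled sample and by grade and gender. For the pooled sample on 7 df, (2.365 + 0.896) × SE gives about 0.30, 0.40 and 0.60 SD at ICC 0.01, 0.02 and 0.05.

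**Limitations.** Add clustering. State also that a school effect does not separate the programme from differences between municipalities, since all intervention schools lie in one.

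**Cost.** Revised wording and one recalculation, with no new data. The price is wider intervals and a less favourable power statement.

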##### Intervention analyses

Annually analyses between intervention and control schools in numerous variables, the sample size for a parallel group design is calculated using *n* = 2 • (σ / Δ) ^2^ • *k* [26]. Here n represents the number of participants in each group, σ (sigma) is the expected standard deviation of the observations (which are assumed equal for all groups), Δ (delta) gives us the relevant difference between observations, and k is the constant in this study chosen based on the common values by a double-sided t-test set at 5% and with test strength 80% (this corresponds to a *k* of 7.9) [26]. Based on these calculations we have determined the sample size to be adequate for all variables for all ages, also when divided into gender (Table 3).

#### Analyses of longitudinal effect

The longitudinal intervention design allows for exploratory analysis of group means over time to discover patterns of systematic variation across groups, as well as among individuals. The design allows for analyses of age and growth effects [50]. As the eldest pupils enrolled at baseline 2015 finish elementary school in 2016, only one year of follow-up is possible. However, an increasing number of years of follow-up are possible with decreasing age at enrolment. This allows for an adjustment of the longevity of being enrolled in the program, and hence measurement of the time-in-the-program effect. Secondly, an annual comparison between the intervention schools and the control schools allows for testing of effect of the intervention. Thirdly, mean values across test time allows for time slopes showing possible effect as an interaction (i.e. effect modification) of intervention and time. A different approach for test across test time may be pre-post analysis of a single follow-up response in conjunction with a baseline measurement [50]. Fourthly, an annual comparison with the upcoming grade within the intervention schools allows for analyses of secular trends.

The longitudinal design in the HOPP study with repeated measures allows for use of a linear mixed regression model using test-year, years of follow-up, intervention versus control school, age and gender as fixed factors for the main outcome of cardio-metabolic risk factors. A similar model may be used for secondary outcomes of academic performance, PA level, cognitive performance, as well as medical and physical results, and simultaneously controlling for baseline values. In addition, the design admits analyses of interaction (i.e. effect modification) between type of intervention group and number of years in intervention.

#### Ethical considerations

Procedures and methods used correspond to the ethical guidelines defined by the World Medical Association’s Declaration of Helsinki and subsequent revisions [51]. The Regional Committee for Medical Research Ethics approved the study protocol (2014/2064/REK south-east) and the study is registered in Clinical trials (ClinicalTrials.gov Identifier: NCT02495714). Informed consent was obtained from all parents prior to testing. No identifiable data is to be published.

The HOPP study is exposed to three challenges regarding the sample size; 1) unexpected dropouts of pupils across years, 2) calculated dropouts of pupils to junior high school, and 3) drop-ins as the control schools may introduce similar interventions. However, the control schools do currently not have any PA program or plans for establishing any such program.

## Discussion

In the western world with increasing inactivity and obesity increasing PA in children is a goal in itself. To counteract health related problems in childhood, school-based PA programs may become an important tool [8, 9, 52, 53]. There are studies showing that an increase in PA may simultaneously improve academic performance even without a pedagogical approach included in the activity [54]. A strategy combining academic learning with increased PA may subsequently improve both academic performance as well as physical health in the childhood population [8, 9, 52, 53]. The ability to reach all socioeconomic layers of the population is a great strength of school-based PA programs as it may contribute to reduce social inequalities in health.

Waters et al. demonstrated that child obesity prevention programmes were effective at reducing adiposity, although not all individual interventions were effective [10]. A recent review by Mura et al. assessing 47 school based RCT ‘s on PA interventions also showed promising positive results for cardio-metabolic variables and physical fitness [7]. A longitudinal study permits the intervention to work over time and may create habitual processes in the pupil’s everyday school life.

Lately two Cochrane reports included several studies focusing on health results from schools based RCT’s [9, 52]. Primary outcomes were rate of moderate to vigorous PA (MVPA) during the school day, time in MVPA during school day and time spent in front of a screen. Secondary endpoints were blood pressure, cholesterol levels, BMI, peak oxygen uptake and heart rate [9]. The reports displayed positive health effects, hence school based interventions were recommended [52]. However, as forty-four studies were ranked in four quality levels, none were ranged above “low quality” [9]. The 2013 report showed a positive effect in more time spent in MVPA, less time in front of a screen, higher VO_2max_ and reduction in serum cholesterol values. The effect sizes were small on all outcomes, and Dobbins et al. warn that despite the inclusion of several RCT’s with a large number of participants, a moderate risk of bias is present and any interpretation should be done with caution [9]. Both reports concluded that additional research on the long-term effect is warranted [9, 52]. The longitudinal design in the HOPP-study addresses this issue by allowing follow-up of 6 years for the youngest children.

Most school based PA intervention studies focus on risk factors of cardio-metabolic disease and academic performance, however, few studies have included measurements of psychological and cognitive outcomes [7]. A review study by Taras et al. found short-term effect on academic results after intervention of increased PA, but uncertainty regarding the long-term effects [54]. Singh et al. found a positive link between participation in PA and long-term effects on academic results [8]. Martin et al. investigated lifestyle changes for overweight children and its effect on academic results in a meta-analysis [53]. The conclusion was despite the lack of clear results, many children profit academically from school based lifestyle interventions. However, better-designed studies are needed to investigate the association between academic, cognitive and physical outcomes with overweight and obese children [53]. The longitudinal design in HOPP permits investigation of long-term associations between PA and cognitive and academic results. The HOPP intervention with its increased PA level is believed to have a significant impact on the children’s cognitive skills. The use of standardized cognitive and academic tests in association with objective assessment of PA level admits valid evaluation of the outcome.

Children, who spend one third of their lives at school, develop significantly more traits than physical lifestyle and academic skills during their school years. Therefore, it is surprisingly few studies who include measurements of emotions, nutrition intake and quality of life [7]. Studies do show effects of exercise beyond improvements in physical fitness and body composition, as in mental wellbeing, psychosocial outcomes and behavior [55]. The present study acknowledges this lack of information and has included standardized tests mapping quality of life (ILC) for all participating children. In addition, age-specific tests of mental health (SDQ) as well as questionnaire concerning body image (SPPA).

Earlier studies have suffered from limited number of participants and study length. Most studies in the review of Singh et al. [8] had a cross-sectional design [56–65], few were interventional studies [18, 66–68], and a only two had a longitudinal design [18, 59]. Both Lees et al. and Mura et al. conclude that larger school-based PA interventions are needed and should focus on cognitive abilities, psychosocial functioning and behavior as well as cardio-metabolic risk factors [7, 55]. The overall conclusion is that several smaller studies display a positive effect of school-based PA programs, however, few large longitudinal studies have been completed to demonstrate similar findings. HOPP, with its longitudinal design and large sample size across six grades, has an ability to evaluate the effect of school-based PA program over time, mainly on cardio-metabolic risk factors, but also in several other variables. The results may therefore yield necessary knowledge to provide a foundation for policy making and future guidelines regarding PA in school. Implementation of health promoting behaviour in elementary schools, with the prospect of reaching all socio-economic layers in a child population, may have the possibility of preventing lifestyle related diseases. Doing so, school-based PA program in elementary schools may have the potential to even out socioeconomic inequalities in public health. The benefits may potentially be large as these diseases are regarded as a major concern against public health [9, 52, 53].

The society may experience severe socioeconomically consequences if non-commensurable diseases increase further, as the cost of treating these diseases vastly exceeds the cost of preventing them. Implementing a school-based PA program as lifestyle adjusting measure is not expensive. A comprehensive schooling of teachers beyond prerequisite education in school-based PA program is required, as well as establishing a set of teaching material. However, these measures are only implemented once and therefore have limited economical consequence. With its longitudinal design, HOPP may be able to disclose effective strategies to reduce cardio-metabolic risk factors in a child population in an affordable way. If positive findings are revealed as an effect of HOPP, a national implementation of increased daily PA in elementary schools may have an profound effect on current and future public health.

